### 2.3 Sample size calculation

A previous study on a treatment to improve insight in schizophrenia [42] observed a mean effect size of 0.51 (standardized mean difference). We used this effect size for our power analysis. Sample size was computed using the program developed by [name] (Harvard School of Public Health) http://hedwig.mgh.harvard.edu/biostatistics/software.Using the estimated effect size of 0.51, this yielded a total number of 128 patients, with a power of 0.80.

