### 2.4 Materials

#### 2.4.1 REFLEX treatment protocol

REFLEX encompasses three modules of four one-hour group sessions each. Module I "Coping with Stigma" focuses on coping with stigmatizing beliefs. The impact of stigmatizing beliefs is discussed and stigmatizing beliefs are disputed and replaced with functional reality-based beliefs about the self. Patients learn that a diagnosis is just a label, saying little about them.

The goal of this module is twofold: first, we presume that denial to cope with the threat that mental illness poses on the self-esteem will be less necessary when the idea of having a mental illness is perceived as less threatening. Following this train of thought, challenging stigmatizing beliefs will ultimately contribute to better insight. Second, with the inclusion of the stigma module we want to prevent an increase of depression to co-occur with increasing insight, as literature has shown that stigma mediates the relationship between insight and mood. In the module "you and your personal narrative" self-reflection is the central theme. Subjects reconstruct their personal narrative, reflect on important changes in their lives and their personal strengths and weaknesses. By offering very structured exercises with clear instructions, REFLEX compensates for cognitive impairments that are thought to hamper self-reflection in schizophrenia. In this module, subjects start practising perspective-taking. Subjects are instructed to ask themselves on a regular basis what other people would think about their thoughts and to check this with an important other. In the third module, called "you in the present", reflection about ongoing thoughts and feelings is stimulated. Between sessions, subjects monitor their thoughts and feelings in their daily life by experience-sampling [43]. In response to a random signal (beeping of a watch) provided six times a day, patients write down the answer to a fixed number of short questions that stimulate self-reflection in a diary. Examples of these questions are: "what was I thinking about before the alarm went off?" and "what would other people think about this thought?". During group sessions, the content of these dairies is discussed. In addition, group exercises and movie vignettes are used to practice perspective-taking during treatment sessions.

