#### 2.4.2 Control condition

The control condition of our study consists of twelve group sessions of standardized 'drill and practice' exercises to cognitive functioning. Exercises were adopted from Cognitive Remediation Training protocol [44] that aims to improve cognitive functioning by combining errorless learning (by using tasks varying from extremely easy to easy), immediate feedback, and targeted reinforcement to enhance flexibility, working memory, and planning. Only exercises targeting cognitive functions that are not associated with insight were selected, trainers did not provide feedback on subject's performance.

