### 2.5 Procedure

Patients who fulfill the inclusion criteria, will be invited to participate in the study. If a patient is willing to participate, study procedures will be explained in detail and after a period of two weeks written informed consent is obtained. Subsequently, diagnosis is verified by the Mini Plus, a semi-structured interview to assess DSM IV pathology [53]. Thereafter, patients are randomly allocated to REFLEX or control condition. Randomization procedures start when the required number of patients per center (ranging from 17-19) are included, or when the first patients was included more than six weeks ago while >10 people are included.

Randomization is centrally coordinated by the Trial Coordination Center of the University Medical Hospital Groningen. The project coordinator gives the subject a unique code and these codes are entered for each patient into a computerized systematic program by an independent researcher. Results of the randomization process are passed to the project coordinator in sealed envelopes and distributed to the on-site therapists. Subsequent subjects are randomized in blocks of two or four, to ensure that the number of patients will be balanced over conditions. Assessment takes place before (T1), directly after (T2) and six months after the training (T3). Assessors are not aware of the condition (control or treatment) the subject is in. During the entire trial patients receive treatment as usual, with the exception of cognitive behavioral therapy.

All fMRI scans will be made in the Neuroimaging Center of the UMCG in Groningen, right before (T1) and directly after (T2) treatment. For geographical reasons, recruitment for the fMRI study is limited to the institutions located in the North of the Netherlands: GGZ Drenthe, Assen; UMCG and Lentis, Groningen, and GGZ Friesland, Leeuwarden. Patients who participate in the fMRI study will be randomized separately.

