## 3. Statistical analysis

### 3.1 Behavioral data

Analysis will be performed according to the *intention to treat principle*. Differences in scores on each of the dependent variables will be examined for T1-T3. The significance of possible differences will be tested with logistic multilevel modeling [54] with the condition (REFLEX or Control) and treatment phase (T1-T3) as levels. A model will be built for each of the dependent variables. Dummy variables will be created for each level and the statistical significance of the regression effects will be tested using the approximate t-test. The dummy variables and their interaction are entered as fixed effects in the model. As random effects, the between-individual and within-individual variance were estimated. All models will be built using the program MlwiN.

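### Both arms are treated in groups, but the model stops at the patient and the 128 assumes independent patients; any positive within-group correlation makes the arm comparison too optimistic

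*Protocol article*

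**What the plan says.** Both treatments are group treatments. Section 2.4.1 states: "REFLEX encompasses three modules of four one-hour group sessions each". Section 2.4.2 states: "The control condition of our study consists of twelve group sessions".

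Section 2.5 describes individual randomization of batches of patients per centre. A batch is randomized once 17 to 19 patients are included, or once more than 10 are included and the first joined over six weeks earlier. Allocation is balanced: "Subsequent subjects are randomized in blocks of two or four, to ensure that the number of patients will be balanced over conditions".

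Section 3.1 enters condition, treatment phase and their interaction as fixed effects, and then fixes the variance structure: "As random effects, the between-individual and within-individual variance were estimated". No therapy-group level is named. Regression effects are tested with an approximate t-test whose degrees of freedom are not stated.

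Section 2.3 gives the sample size: "Using the estimated effect size of 0.51, this yielded a total number of 128 patients, with a power of 0.80". It mentions no ICC, group size or design effect.

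**The concern.** Members of a therapy group share trainers, sessions and each other for twelve sessions. For REFLEX, section 2.4.1 makes this part of the treatment: diaries are discussed in the group and perspective-taking is practised in group exercises. Scores after treatment may therefore be more alike within a group than between groups.

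Such group effects arise after randomization and are nested within arm, so they add directly to the variance of the arm contrast at T2 and T3. Randomizing within centre balances centre effects but does not remove this component. A model that ends at the patient counts 128 independent patients where there may be only about 16 groups.

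At stake is the REFLEX-versus-control comparison on every primary outcome, because section 3.1 uses the same model for each dependent variable.

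This is not a detail left to a fuller document. The article names its variance components, and they stop at the patient.

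**Working it through.** **Inputs from the document.** Effect size d = 0.51, power 0.80, N = 128 (section 2.3); eight centres (section 2.2); balanced arms and batch sizes (section 2.5); random effects (section 3.1).

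**Assumptions, not in the document.** Two-sided alpha 0.05; 64 per arm; no dropout; continuous scores with SD 1, as a standardized mean difference implies; correlation 0.5 between a patient's repeated scores; therapy-group ICC 0.01 to 0.10. Group size m = 8 follows from one group per arm per centre: 128 / (8 × 2) = 8.

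**Step 1: the plan's own figure.** The noncentrality is 0.51 × √(64/2) = 2.885. With 126 df, power is 0.817. At d = 0.51, 80% power needs 62 per arm, or 124 in total; at d = 0.50 the same calculation gives exactly 64 per arm, or 128. The stated figure is therefore an independent-patients result. The slack is 128/124 = 1.03, which a design effect with m = 8 uses up at ICC = 0.03/7, about 0.005.

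**Step 2: design effect and power, groups of 8.** DE = 1 + (m − 1) × ICC; noncentrality = 2.885/√DE. Power is shown with 126 df (design effect alone) and with 16 − 2 = 14 df (group-level test).

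| ICC | DE | Effective N = 128/DE | Power, 126 df | Power, 14 df |
|---|---|---|---|---|
| 0 | 1.00 | 128 | 0.817 | 0.765 |
| 0.01 | 1.07 | 120 | 0.790 | 0.737 |
| 0.02 | 1.14 | 112 | 0.765 | 0.710 |
| 0.05 | 1.35 | 95 | 0.693 | 0.637 |
| 0.10 | 1.70 | 75 | 0.593 | 0.540 |

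The first row separates two effects: 0.817 − 0.765 = 0.052 is the price of 14 df with no clustering at all.

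**Step 3: type I error of the planned test, groups of 8.** As an approximation, 2 × (1 − Φ(1.96/√DE)) gives 0.058 / 0.066 / 0.092 / 0.133 for ICC 0.01 / 0.02 / 0.05 / 0.10. Simulating the condition × T2 contrast in a patient random-intercept model (20,000 trials per setting, group effect at T2 and T3) gives 0.061 / 0.069 / 0.098 / 0.149, and 0.051 at ICC 0. The simulated values are slightly higher because the pooled residual also uses T2 versus T3, from which the shared group effect cancels. At ICC 0.10, separate simulations ranged from 0.13 to 0.16, so about 0.14 is a fair summary.

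**Step 4: more favourable settings, ICC 0.05.**
- Groups of 5, which the second randomization trigger allows: DE = 1 + 4 × 0.05 = 1.20; type I error 0.074 by the formula, 0.080 simulated. Power is 0.743 from the design effect alone, and 0.714 with about 24 group-level df (128/5 − 2 = 23.6).
- Groups of 8, clustering in REFLEX only: the variance of the contrast grows by (1.35 + 1)/2 = 1.175; type I error 0.071 by the formula, 0.076 simulated.

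**The case against.** A reader might infer that type I error is inflated and that 0.80 power is not delivered, full stop. The document does not support that, for these reasons.

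- **No ICC is given.** At 0.01 the type I error is about 0.06 and power, before any loss of degrees of freedom, is 0.79. At that end the damage is slight.
- **The lowest power figures mix two things.** About 0.05 of the fall to 0.74 / 0.71 / 0.64 / 0.54 comes from testing on 14 df, not from clustering.
- **Group size is inferred.** The document does not state the number of groups per arm, and the trigger of more than 10 patients allows groups of about 5 or 6.
- **Equal clustering in both arms is not established.** Group discussion and group exercises are described for REFLEX. The control arm is standardized drill and practice without trainer feedback on performance.
- **The power figures are for a post-treatment comparison, as in section 2.3.** If scores were adjusted for baseline at correlation 0.5, the variance factor would be 0.75 + 7 × ICC, and 14-df power about 0.81 / 0.73 / 0.61 at ICC 0.02 / 0.05 / 0.10. An unadjusted change score gains nothing at that correlation, since 2 × (1 − 0.5) = 1. Section 3.1 does not describe baseline adjustment.

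All of this stands as a limit on size and certainty. None of it removes the core: for any positive group ICC the error runs in one direction, towards standard errors that are too small, and the document gives no reason to take the ICC as zero.

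It is also tempting to conclude that the trial needs more patients. Under equal clustering in groups of 8, 124 × DE would give about 142 / 168 / 211 at ICC 0.02 / 0.05 / 0.10. Those totals rest wholly on assumed inputs, so they do not show that 128 is inadequate.

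**Conclusion.** The point holds in conditional form. The plan delivers both arms in groups, fixes a model without a group level, and sizes the trial as if patients were independent. If outcomes are positively correlated within therapy groups, the planned test rejects a true null too often, and the stated 0.80 has slack only up to an ICC of about 0.005 with groups of 8.

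Over an assumed ICC of 0.01 to 0.10, equal in both arms, with 16 groups of 8, type I error runs from about 0.06 to 0.14. Power runs from 0.79 to 0.59 through the design effect alone, or from 0.74 to 0.54 with group-level degrees of freedom. With groups of about 5, or clustering mainly in REFLEX, type I error at ICC 0.05 is nearer 0.07 to 0.08 than 0.10. The direction follows from the design; the size rests on an ICC and a group structure that the document does not give.

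**What to change.** - Record a therapy-group identifier for every patient in both arms.
- In section 3.1, add therapy group as a random effect at the post-baseline occasions (T2 and T3), and allow its variance to differ between REFLEX and control.
- Test condition × phase with small-sample degrees of freedom, for example Satterthwaite or Kenward-Roger. A t-test on group means is a simple check.
- In section 2.3, restate the power of 128 patients with DE = 1 + (m − 1) × ICC over a stated range of ICC and group size, and give the degrees of freedom used.

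The cost is one extra data field, a few lines of analysis text, a less favourable power figure and slightly wider intervals. No extra patients are needed, and neither treatment nor assessment changes.

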### 3.2 fMRI

Scans will be acquired using a 3T Phillips Intera Quaser (Best, The Netherlands) equipped with a synergy SENSE eight-channel head coil. Functional images are acquired using a T2*-weighted echo-planar sequence with 37 interleaved axial slices oriented approximately 10-20° to the ac-pc transverse plane, a thickness of 3.5 mm and no slice gap to cover the entire cortex (TR = 2 s, TE = 35 ms, flip angle = 70 degrees, FOV = 224 mm, 64 × 64 matrix of 3.5 × 3.5 × 3.5 voxels). In addition, two T1-weighted 3-D fast field echo (FFE) anatomical images (voxel size, 1 × 1 × 1 mm) containing 160 slices (TR = 25 ms; TE = 4.6 ms; slice-thickness = 1 mm; 256 × 256 matrix; FOV 26 cm) will be acquired parallel to the bicommissural plane. Data will be preprocessed using the Statistical Parametric Mapping software package (SPM8, Wellcome Department of Cognitive Neurology, London, UK: http://www.fil.ion.ucl.ac.uk) in the following order: functional images will be corrected for slice timing, realigned to the first volume of the first run to correct for shifts in head position and coregistered to the anatomy. Coregistrations were controlled manually for each subject to ensure correct coregistration. Functional images were spatially normalized based on the basis of the MNI (Montreal Neurological Institute) T1 template and then spatially smoothed with a 10 mm full-width half-maximum (FWHM) isotropic Gaussian Kernel. Preprocessed data will be analyzed to calculate the main effects of Condition and the two-way interaction of Condition x Phase.

## 4. Discussion

REFLEX may have a potential for improving insight in patients with schizophrenia. Our design offers the opportunity not only to examine the results of REFLEX at a behavioral level, but takes underlying changes in brain activation into account as well. With the study, we hope to contribute to the existing knowledge of what mechanisms are underlying changes in insight in schizophrenia. Improving insight in schizophrenia is a challenging task that needs careful consideration. During the development of the intervention, some clinicians addressed that patients might become more depressed if their insight would improve. Although the evidence for the development of depression is not conclusive [23], we paid special attention to this issue. As was explained in the introduction of this paper, there is evidence that this risk concerns patients with internalized stigma. By including a module that aims to reduce internalized stigma, we feel we have minimized this potential risk. Second, by definition, patients with impaired insight often do not feel they need treatment and will not spontaneously enroll in a therapy trial to improve their insight. Therefore, a common language needed to be developed. We cannot simply give patients a phone call, tell them that they are mentally ill and not fully aware of this and expect them to participate in our study. Instead, patients will be explained that being under treatment in a mental health institution brings about a lot of changes in their daily lives. REFLEX may help them to recognize these changes and gain more control over their lives. In a previous and unpublished pilot study we found that explaining the aim of REFLEX in comparable phrasing was acceptable to most patients and made them consider participation. Third, a methodological problem that is associated with insight is that most assessment instruments are based upon the traditional medical model: patients have to use the same terminology as their psychiatrists to be considered insightful. This approach ignores the insight some patients demonstrate, when they are able to describe the problems they experience in daily life and to attribute these problems to a mental illness. If they do not use the term "psychosis" or "schizophrenia" to describe their mental health, their insight is rated as impaired by most of the current instruments. However, this may be just a discussion about labels and not about actual insight. We hope to have solved this problem by including scales that measure the preconditions of insight, such as the BCIS that measures cognitive insight, to traditional insights scales. The BCIS does not measure agreement insight in and medical way, but takes into account how patients perceive their own thoughts and feelings. Finally, care as usual for people with schizophrenia in the Netherlands is extensive. Psycho-education, Liberman training modules (social skills), and CBT are accessible for most patients. Because of this extensive care, it is very hard to obtain treatment effects over and above the effect of care that is already provided. However, several studies have shown that specific interventions can make a significant contribution to relevant outcome measures [55,56]. Through the unique focus in REFLEX on the improvement of self-reflectivity and perspective taking abilities and by that improving insight we expect to make a significant contribution to the well-being of people with schizophrenia.
